### Timeline

This study will include 2 types of observations: continuous passive monitoring and active surveys conducted at specific time points. Passive monitoring will occur continuously for 6 months in both groups, followed by an additional year for participants with SUD after their discharge from the treatment facility. Active surveys will be conducted at three time points: (1) baseline session or baseline, (2) 3 months after baseline, and (3) 6 months after baseline.

For digital monitoring purposes, smart bands provided to participants will be synchronized with a smartphone at the baseline session. Psychological assessment will be conducted within the first 15 days after baseline. Retesting will take place during the 15 days prior to the 6 months after baseline. Emotional reactions to cravings will be assessed at two points: (1) 3 months after baseline and (2) at 6 months after baseline (Figures 1A-1F).

**Figure 1 figure1:**
[figure not shown]
Timeline of experimental procedures. (A) Demographic and psychological assessment, a battery of interviews and tests will be applied at 2 timepoints. (B) Digital measurements with the smart band Xiaomi Redmi Smart Band 8, starting on day one for controls, and after the first month of treatment for substance use disorder. (C) Evaluation of the emotional state during craving halfway through the digital monitoring period (third month), and at the end of it. (D) Data preprocessing is required for all 3 data sources. (E) Training in a machine learning predictive model in neural networks. (F) creation of a graphic user interface for clinical use.

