### Demographic and Psychological Assessment

Demographic information, such as age, place of birth, education, occupation, civil status, household income, housing characteristics, as well as medical and family history, will be collected at baseline. A form will be filled in by the participant, assistance from the trained research staff will be provided if it is required.

The psychological tests will be administered at baseline within the first 15 days of participation. A battery of self-report questionnaires has been chosen to assess for a history of childhood trauma (Adverse Childhood Experiences Assessment [ACEs]) [68], the presence of depression or depressive symptoms (Beck Depression Inventory [BDI-II]) [69], anxiety and stress (Beck Anxiety Inventory [BAI-II]) [70], sleep disorders (Pittsburgh Sleep Quality Index [PSQI]) [71], and short-term memory (Wechsler Adult Intelligence Scale IV [WAIS-IV] subtests: Digit Span and Letter-Number Sequencing) [72]. Substance use–specific tests will aim to determine the type of substance, frequency and quantity of used drugs (Alcohol, Smoking and Substance Involvement Screening Test [ASSIST]) [73], level of substance craving (Mannheimer Craving Scale [MaCS]) [74], as well as the stage or frame of mind of the individual starting the therapeutic process (University of Rhode Island Change Assessment Scale [URICA]) [75].

To obtain a comparative measurement after treatment, depression, anxiety and stress, sleep disorders, short-term memory, stage of change and craving, will be reevaluated within fifteen days before the sixth month period of digital tracking ends (Figure 3).

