**Figure 5 figure5:**
[figure not shown]
Model’s possible outputs. These categories will be used as output labels of the predictive model and will allow the evaluation of the patterns detected from the input.

For the duration of the therapeutic process, the following labels will be used:

Timely rehabilitation: patients with SUD who complete the rehabilitation protocol within 7 months.Late rehabilitation: patients with SUD who complete the protocol in 7 months or longer.

Regarding relapse latency, the labels will include the following:

Early relapse: substance use occurring within the first 6 months post discharge.Late relapse: substance use occurring after 6 months but before the completion of 18 months post discharge.One-year maintenance: patients who have abstained from substance use at the end of the 18-month postrecovery period.

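### The timely/late duration output has no prediction time, and its stated inputs include an end-of-treatment retest, a second craving session and post-discharge band data

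*Protocol article*

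**What the plan says.** **Calendar.** The Figure 1 legend has band measurement "starting on day one for controls, and after the first month of treatment for substance use disorder". The Timeline section adds that "smart bands provided to participants will be synchronized with a smartphone at the baseline session", which ties baseline to the start of the band. The craving image test is done 3 and 6 months after baseline; the Figure 1 legend describes this as "Evaluation of the emotional state during craving halfway through the digital monitoring period (third month), and at the end of it". For the psychological battery, "Retesting will take place during the 15 days prior to the 6 months after baseline". The Demographic and Psychological Assessment section repeats that these measures "will be reevaluated within fifteen days before the sixth month period of digital tracking ends", and gives the purpose as a comparison once treatment is over. Monitoring of SUD patients is then "followed by an additional year for participants with SUD after their discharge from the treatment facility". The abstract gives the total as 18 months, 6 in rehabilitation and 12 after discharge.

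**Labels.** Under Output (Figure 5), timely rehabilitation means "patients with SUD who complete the rehabilitation protocol within 7 months" and late rehabilitation means "patients with SUD who complete the protocol in 7 months or longer". The text does not say when the 7 months begin.

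**Inputs.** The Objective names one set of sources (digital measurements, psychological profiles, facial emotion recognition, emotional state during craving) for both therapy duration and relapse. Data Preprocessing scales and integrates everything from the wearable, the psychological assessment and the craving assessment, and filters features by their correlation with the target. Predictive Model makes duration an output and requires AUC and F2 of at least 0.8. None of these sections gives a prediction time.

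**The concern.** A model that forecasts how long treatment will last may use only what is known before that length is settled. The stated inputs include data collected at the end of treatment and for a year after it. A patient who completes early would either lack the second craving session or take it after discharge, and would have a shorter in-facility band record. Either feature can reveal the label without carrying any prognostic information. The correlation filter would tend to keep such features.

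The thresholds decide whether the model counts as fully functional, and the AUC threshold triggers construction of the clinical interface. If the duration AUC draws on late data, the threshold could be passed without any demonstration of advance prediction. In the clinic, the forecast would arrive when completion within 7 months is nearly or already decided.

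**Working it through.** **Inputs from the protocol**

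- Band start in the SUD group: after treatment month 1 (Figure 1 legend).
- Baseline: the session at which the band is synchronised (Timeline).
- Craving sessions: 3 and 6 months after baseline (Timeline).
- Retest: the 15 days before month 6 after baseline; 15 / 30.4 = about 0.5 month.
- Duration cut: 7 months, origin not stated (Output).
- Monitoring of SUD patients: 6 + 12 = 18 months, which reproduces the stated total.

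**Formulas.** Treatment month of an event = treatment month of baseline + months after baseline. Lead = treatment month of the cut − treatment month of the event.

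Three readings are possible:

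- A: baseline at treatment month 1, cut counted from treatment start, so at month 7.
- B: baseline at treatment month 1, cut counted from baseline, so at 1 + 7 = month 8.
- C: baseline on treatment day 1, cut at month 7.

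| Reading | Session 1 | Lead | Session 2 | Lead | Retest | Lead |
|---|---|---|---|---|---|---|
| A | 1 + 3 = 4 | 7 − 4 = 3 | 1 + 6 = 7 | 7 − 7 = 0 | 6.5 to 7 | 0 to 0.5 |
| B | 1 + 3 = 4 | 8 − 4 = 4 | 1 + 6 = 7 | 8 − 7 = 1 | 6.5 to 7 | 1 to 1.5 |
| C | 0 + 3 = 3 | 7 − 3 = 4 | 0 + 6 = 6 | 7 − 6 = 1 | 5.5 to 6 | 1 to 1.5 |

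If session 2 shares the retest visit, which is not stated, its lead has the same range as the retest. The Figure 1 legend and the Timeline together favour baseline at treatment month 1 (A or B). They do not choose between A and B.

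**What needs no clock.** A patient discharged on completion has a fixed duration label at discharge. Everything collected in the following 12 months postdates that label on all three readings. Besides the band data, this includes the sleep questionnaire that Table 1 repeats at 18 months in the SUD group.

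**Landmark.** Session 1 has 3 to 4 months of lead on every reading. Closing the duration inputs there keeps 3 of 6 in-facility band months (50%).

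**Label boundary.** Completion at exactly 7 months satisfies both duration labels as worded.

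**What cannot be computed.** The effect on AUC depends on how many patients complete before session 2 and how many complete near the cut. The protocol gives no completion times.

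**The case against.** The strongest reply is that this is largely silence in a condensed article. A prediction time for each output could stand in a full protocol or analysis plan that is not shown, and the figures, which might carry a treatment-month axis, are missing from the text at hand. The scaling sentence concerns standardisation and does not say that every time point feeds every output. Output places duration in its own layer, which leaves room for different inputs. The retest has a stated before/after purpose and is nowhere named as a duration predictor.

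Part of this stands: the text does not prove that late data will enter the duration model. It does fix one common list of sources for duration and relapse, integrates all of it, and dates some of it after the outcome. Carrying out the text as written would admit these data, so the point is more than an omitted detail.

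Three stronger readings are tempting and should not be drawn:

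- **The late assessments have no lead at all.** That holds only on reading A. Reading A also fits the labels poorly: with 6 monitored months in rehabilitation after a first unmonitored month, a patient on schedule completes no earlier than about month 7, and the timely class is nearly empty.
- **Two thirds of the band data leak.** The ratio 12/18 = 67% is a share of planned monitoring time. It does not measure leakage, and no section says that post-discharge data will predict a completed duration.
- **The late data can safely be moved to the relapse labels.** The Withdrawal Criteria and Data Exclusion sections end participation at relapse. The length of the post-discharge record would therefore reveal the relapse label, and the same fault would recur there.

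**Conclusion.** The point holds as a design weakness that should be corrected before modelling. As written, the duration output may draw on post-discharge data that postdate its label on any reading, and on a retest and second craving session that precede the 7-month cut by 0 to 0.5 month (reading A) or 1 to 1.5 months (readings B and C). An AUC of at least 0.80 from such inputs would not establish advance prediction.

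This rests on three assumptions: that the integrated data set is used for the duration output as the Objective and Predictive Model sections suggest; that discharge coincides with or follows completion; and, for the treatment-month dates, that SUD baseline is the band start in the Figure 1 legend. Confidence is medium, because the origin of the 7 months is undefined and the size of the effect cannot be determined. The overlap at exactly 7 months is real but minor.

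**What to change.** 1. State the treatment day of baseline and the origin of the 7 months, and reword the labels as *under 7 months* and *7 months or longer*.
2. For the duration output, use only inputs dated up to craving session 1, among patients still in treatment at that time. Report earlier completers separately.
3. For the relapse labels, session 2, the retest and in-facility band data may be used, with inputs closed at discharge. Record the treatment day of session 2 so that its position relative to discharge is known.
4. Keep post-discharge band data out of the relapse classifier unless they are cut at a fixed landmark among patients still relapse-free at that landmark.

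**Cost.** Protocol wording, date filters and one recorded date; no new data collection. The duration model keeps the baseline battery, session 1 and 3 of 6 in-facility band months. It loses session 2, the retest and the other 3 months, so its AUC may be lower. The 18 SUD patients enrolled by June 2025 can be handled from recorded dates, assuming that the facility holds their treatment start dates. The article reports the data as still at labelling and preprocessing, so the rule can be set before any model is trained.

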### Participants and Study Setting

#### Sample Size

The minimum sample size was determined using Epidat 4.2 software (Xunta de Galicia), following the equation for estimating the comparison between independent means. The calculation was based on data reported by Rykov et al [30], in a study where patients were screened using wearable devices, and (MLMs were applied (Textbox 1).

Sample characteristics.Variance: distinctStandardized mean difference=2.54Expected SD of population 1=1.6Expected SD of population 2=3.21Ratio between sample sizes=1CI=95%Statistical power=80%

In addition, based on the rule of one-to-ten for artificial neural network (ANN) models suggested by Kavzoglu and Mather [31], in which a sample should be at least 10-100 times the numbers of independent variables (4 in this study, based on the 4 suggested profiles), a sample of 40-400 participants was obtained. Therefore, a minimum sample size of 25 was determined for each group. Participants will be recruited within 2 years of the beginning of the study, aiming for recruitment greater than 25 per group.

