Machine learning (ML) has also been used as a tool for the diagnosis of anxiety disorders with the use of speaking patterns, gaming activities, and self-reports [40-49]. It has also allowed researchers to measure the severity and variability of that disorder in varying environments through wearables, allowing remote intervention and through simulations [30,48,50-52]. It has also been used in predictive models for early depression diagnosis through smartphone use, severity, and progression through physical activity, sleep, and social interaction data [53-61]. In addition, ML models (MLM) have been trained to detect relapse in MDD and risk of suicide [62-64]. Similarly, it has been used to predict the start of a psychotic episode 5 days before it by using patterns of movement and sleep disturbance [63,65].

With a 60% relapse rate, an average of 5 recovery attempts required for full remission, and a growing number of new patients with SUD presenting at younger ages [2], this disorder represents a significant opportunity for digital health technologies. These tools, often used in managing cognitive and mood disorders commonly comorbid with SUD, have the potential to enhance treatment effectiveness and reduce relapse rates.

This study aims to integrate physiological, behavioral, and psychological data through digital technologies to develop comprehensive digital profiles of individuals with SUD. These profiles will be analyzed using ML tools to identify clinically relevant patterns. The resulting models are intended to serve as complementary tools in clinical practice, supporting treatment decisions, improving prognostic accuracy, and facilitating the monitoring of patients in remission.

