### Output

The primary objective of this study is to develop a MLM capable of predicting clinical outcomes in patients. To achieve this, the data will be segmented and classified into 5 categories (Figure 5). Around 2 of these categories will correspond to the first layer, which pertains to the duration of the therapeutic process, while the remaining 3 will focus on the latency of relapse, if any.

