## Discussion

### Principal Findings

This study aims to evaluate the viability and efficacy of a predictive model designed to estimate the duration of a rehabilitation process and predict the likelihood of early, late, or no relapse in substance use, based on the digital phenotype of SUD. The hypothesis posits that an AUC of ≥0.80 and F2 of ≥0.8 will demonstrate that data collected from an affordable commercial smart band, demographic questionnaires, psychological tests included in the institution’s base protocol, and the proposed use of FER combined with valence and emotional activation scoring during craving episodes can effectively support the creation of this predictive model.

The potential of this project is supported by several premises. Wearable devices have become increasingly accessible and seamlessly integrated into daily life. As of January 2024, GSMA Intelligence reported 125.4 million cellular connections in Mexico, and GWI estimated that 31% of internet users aged 16-56 years use a smartwatch or smart band [81]. Considering that the device used in this study is among the most affordable commercial smart bands and compatible with any mobile operating system, the development of a viable predictive model could introduce this tool as a complementary aid in SUD rehabilitation, enhancing the effectiveness of treatment strategies.

Wearable devices and MLM have been successfully applied to various mental health conditions. For example, passive physiological activity measurements and MLMs have distinguished depressive patients from healthy controls by correlating variations in circadian rhythms, nocturnal HR, and higher depression test scores [30]. Similarly, MLMs using passive data have predicted depressive, manic, or hypomanic episodes in patients with bipolar disorder (BD) by identifying sleep disturbances, circadian rhythm changes, and physical activity variations [82]. Furthermore, facial emotion recognition combined with MLMs has been used to diagnose and predict alexithymia with an AUC of 0.80 [83]. In the context of SUD, MLMs have demonstrated potential by evaluating participant engagement, correlating stress and craving during recovery, and providing insights into treatment outcomes [84].

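### The sample-size argument supports only the SUD-versus-control comparison, not outcome prediction within SUD patients, and its stated inputs do not give 25 per group

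*Protocol article*

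**What the plan says.** The Protocol article's Sample Size section gives two bases for the number of participants.

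- **Mean comparison.** The minimum was obtained in Epidat "following the equation for estimating the comparison between independent means". The inputs are unequal variances, a difference of 2.54 labelled as standardized, SDs of 1.6 and 3.21, ratio 1, a 95% confidence level and "Statistical power=80" percent. They are taken from a wearable-device study. The Principal Findings section, citing the same reference, says of that work that "passive physiological activity measurements and MLMs have distinguished depressive patients from healthy controls".
- **Rule for neural networks.** Ten to 100 times four profiles, from which "a sample of 40-400 participants was obtained".

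The section then concludes that "a minimum sample size of 25 was determined for each group" and says recruitment will aim higher.

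The Output section states: "The primary objective of this study is to develop a MLM capable of predicting clinical outcomes in patients". The labels listed with Figure 5 are timely or late rehabilitation, early relapse, late relapse and one-year maintenance. One example is "Early relapse: substance use occurring within the first 6 months post discharge". Under Validation and Verification and under Predictive Model, success is an AUC of at least 0.80 and an F2 of at least 0.8.

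**The concern.** The calculation answers a different question from the primary one. It compares the means of two equal groups. The labels to be predicted describe how long a patient's rehabilitation takes and whether and when he relapses after discharge. A control can hold none of them, and controls are followed for only 6 months. For the primary objective the usable number is the SUD group alone, divided by outcome.

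A reader who sees 80% power beside a minimum of 25 per group may take the study to be adequately sized for relapse prediction. The protocol goes on to say that the final test result will confirm the models as tools informing clinical decisions, and it plans a clinical interface. The size should therefore be justified for that use, or the protocol should say plainly that it was not.

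**Working it through.** **1. Reproducing the protocol's number.** Inputs from Sample Size: SDs 1.6 and 3.21, ratio 1, 80% power, alpha 0.05. Two-sided testing is assumed, because sidedness is not stated.

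Sum of variances: 1.6² + 3.21² = 12.8641. Pooled SD: √(12.8641/2) = 2.536.

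Normal formula: n per group = (1.96 + 0.8416)² × (sum of variances) / difference², with (1.96 + 0.8416)² = 7.849.

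| Reading of 2.54 | Normal formula | Welch t |
|---|---|---|
| Raw difference | 7.849 × 12.8641 / 2.54² = 15.65, so 16 | 17 gives 79.9%, 18 gives 82.3% |
| Standardized difference | 7.849 × 2 / 2.54² = 2.43, so 3 | 4 gives 78.9%, 5 gives 91.1% |

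Neither reading gives 25. With 2.54 as a raw difference, power at 25 per group is 94.3% (normal) or 93.1% (Welch t), not 80%. One-sided testing gives 13 and 90% power gives 21. Two-sided 95% power gives 26, but 95% is not the stated power. The value 2.54 is almost equal to the pooled SD of 2.536, so its label or its value needs checking.

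**2. The neural-network rule.** 10 × 4 = 40 and 100 × 4 = 400. Both groups together give 25 + 25 = 50, which is inside the range. SUD patients alone give 25, which is below 40.

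**3. Matching each basis to each task.**

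| Task | Who carries the label | Mean comparison applies? | Rule's floor of 40 met at the minimum? |
|---|---|---|---|
| SUD versus healthy | Both groups (50) | Yes | Yes |
| Therapy duration | SUD only (25) | No | No |
| Relapse latency | SUD only (25) | No | No |

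**4. Precision for the primary aim (illustration).** The Introduction reads "With a 60% relapse rate, an average of 5 recovery attempts required for full remission". The 60% is a background figure, not a sizing input. If it is assumed to hold here, 25 SUD patients split into 15 relapsers and 10 non-relapsers.

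Hanley-McNeil standard error at AUC A = 0.80:
- Q₁ = A/(2 − A) = 0.6667; Q₂ = 2A²/(1 + A) = 0.7111; A² = 0.64.
- Variance = [0.16 + 14 × (0.6667 − 0.64) + 9 × (0.7111 − 0.64)] / 150 = 1.1733/150 = 0.00782.
- SE = 0.088, so the 95% interval is 0.80 ± 0.17, about 0.63 to 0.97.

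This lets all 25 patients contribute to testing. The Data Preprocessing section tests on one held-out fold. The number of folds is left open. If it were five (an assumption), a fold would hold about 3 and 2 patients, the SE would be 0.218 and the lower limit about 0.37. The upper limit would exceed 1, so the approximation no longer works at that size.

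**5. Within-SUD power for a mean difference (illustration only).** Take 2.54 as raw, move the two SDs onto outcome classes and use Welch t. A 15/10 split gives 56.8% if the smaller class has SD 3.21, and 70.5% if the larger class does. Splits from 18/7 to 7/18 range from about 41% to 71%.

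**The case against.** The strongest reply is that a two-group calculation fits something the study really plans. The Predictive Model section lists a model separating healthy people from SUD patients, and Study Design says the model relies on comparisons between groups. That stands: the calculation should be kept for that task.

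Next, the article never says that the 80% is for relapse prediction, it calls 25 a minimum, and it aims for more. With 18 SUD patients enrolled by June 2025 and recruitment open until January 2027, the final number may be larger. The limitations section also admits that the model may miss the desired accuracy with the participants recruited. These points soften the concern. None of them says what the 80% refers to or supplies a basis for the within-SUD aim.

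Third, the neural-network rule can be read as the sizing argument for the prediction model. It reaches 40 only by counting controls, who carry no duration or relapse label.

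A reader might also infer that the protocol's own inputs give 57-70% power for the primary aim. The documents do not support that. It takes an assumed 60/40 split where the stated ratio is 1, a raw reading of a value labelled standardized, and SDs transferred to outcome classes. With the labelled reading, power at 15/10 exceeds 99.9%. Success is also judged by AUC and F2, not by a test of one mean. Nor can a reader conclude that 25 came out of the mean formula, since neither reading returns it.

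**Conclusion.** The point holds in this form. Neither stated basis sizes the study for its primary objective: the 80% power belongs to SUD versus control, and 25 SUD patients fall 15 short of the rule's own floor. These two statements need no outside assumption beyond reading the two equal groups of the calculation as SUD and control, which the wording per group and the source study support.

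Separately, 25 per group is not reproducible from the stated inputs (about 16-18 or about 3-5, depending on how 2.54 is read, two-sided).

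The AUC interval of about 0.63-0.97 is the most useful measure of size. It rests on exactly 25 SUD patients, a 15/10 split and every patient being used for testing. More recruitment would narrow it. A single test fold, or loss of data through the withdrawal and exclusion rules, would widen it. At this size a point AUC of 0.80 cannot by itself confirm that a relapse model works. The within-SUD power figures are illustrations and not a property of the design.

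**What to change.** 1. **Sample Size:** correct the label or the value of 2.54, and restate the number per group or the power that follows from it.
2. **Sample Size:** say that this calculation and its power apply only to SUD versus control, and that the number was not derived for prediction within SUD patients.
3. **Sample Size:** for the primary aim, state the expected precision with its assumptions. For example, an AUC of 0.80 with 25 SUD patients split 15/10 has a 95% interval of about 0.63-0.97 if all contribute to testing, and a wider one on a single held-out fold. If a within-SUD power figure is given at all, label it illustrative and list its assumptions.
4. **Validation and Verification, and Predictive Model:** describe the relapse and duration models at this size as development models reported with their interval, not as confirmed because the point AUC reaches 0.80.

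The cost is rewording and a less favourable stated figure for the primary aim. No extra patients or procedures are needed.

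### The minimum of 25 per group does not follow from either stated calculation, and the ten-per-variable rule is not met for the SUD-only duration and relapse models

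*Protocol article*

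**What the plan says.** The Sample Size section of the protocol article offers two justifications.

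- **Two means.** The size was computed "following the equation for estimating the comparison between independent means". Textbox 1 lists distinct variances, a standardized mean difference of 2.54, SDs of 1.6 and 3.21, a 1:1 ratio, 95% confidence and "Statistical power=80"%. The resulting n is not reported.
- **Neural-network rule.** The section says that "a sample should be at least 10-100 times the numbers of independent variables", counted as "4 in this study, based on the 4 suggested profiles", from which "a sample of 40-400 participants was obtained".

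It then concludes "Therefore, a minimum sample size of 25 was determined for each group" and adds an aim to recruit more than that.

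Under Output, the article states: "The primary objective of this study is to develop a MLM capable of predicting clinical outcomes in patients". The labels given with Figure 5 are timely or late rehabilitation, and early relapse, late relapse or one-year maintenance. The first two are defined for patients with SUD, and the other three by time after discharge or recovery. Under Predictive Model, the article adds a classification of SUD patients against healthy individuals.

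**The concern.** The article states a method, its inputs and a result, so a reader should be able to reproduce the result. Three things look wrong.

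1. An effect of 2.54 SDs would be enormous and would need only a handful of participants, so 25 sits oddly beside it. A standardized effect also does not need two SDs listed next to it.
2. The rule's lower bound of 40 can be met by 25 + 25 = 50 only if controls count, but the models named as the primary objective learn from labels that controls cannot carry.
3. The four variables are four profiles, each made up of many measurements.

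At stake is whether the prediction models have any size basis. Their AUC and F2 thresholds of 0.8 lead on to an interface for clinical use.

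**Working it through.** **Inputs (Sample Size, Textbox 1).** SD1 = 1.6, SD2 = 3.21, effect = 2.54, ratio 1, 95% confidence, 80% power. Sidedness is not stated, so two-sided 5% is assumed: (1.960 + 0.842)² = 7.849.

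**Attempt to reproduce 25, with 2.54 as a raw difference**

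n = (z_α + z_β)² × (SD1² + SD2²) / δ²

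- SD1² + SD2² = 2.56 + 10.3041 = 12.8641
- n = 7.849 × 12.8641 / 2.54² = 15.65, so **16 per group**
- Welch noncentral t: power 0.799 at 17 and 0.823 at 18, so **18 per group**
- One-sided 5%: 13 per group (14 by Welch t)

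**With 2.54 as a truly standardized difference**

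- n = 2 × 7.849 / 2.54² = 2.43, so **3 per group**
- By t: 4 with equal SDs. With the stated unequal SDs, power is 0.79 at 4 and 0.91 at 5, so 5.

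**Reverse check at 25 per group**

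- Raw difference of 2.54: power 0.943 (normal) or 0.931 (Welch), against the stated 80%
- Raw difference with 80% power: √(7.849 × 12.8641 / 25) = 2.01 (normal formula), which is 2.01 / 2.536 = 0.79 SD

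**Routes that come near 25, none of them stated in the section**

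| Change | n per group |
|---|---|
| 95% power | 26 |
| α = 0.01 | 24 (Welch 26) |
| SD of 3.21 in both groups | 26 |
| Rule total of 40, i.e. 20 per group, inflated for 20% loss: 20 / 0.8 | 25 |

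**The value 2.54 itself.** √((1.6² + 3.21²) / 2) = √6.432 = 2.536, which rounds to 2.54. As a raw difference, 2.54 is therefore almost exactly one SD (2.54 / 2.536 = 1.00).

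**Ten-per-variable rule**

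- 10 × 4 = 40 as the lower bound
- SUD plus controls: 25 + 25 = 50, which is at least 40, so it is met
- SUD only: 25 is below 40, so it is **not met** for the duration and relapse outputs

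**Count of variables.** The feature column of Table 2 lists 5 physical-activity, 5 heart-rate, 7 sleep and 2 rhythm features: 5 + 5 + 7 + 2 = about 19. These all lie within one of the four profiles (digital biomarkers).

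**The case against.** The strongest defence is that 25 errs on the safe side for the comparison that the formula sizes. It is a minimum, the aim is to exceed it, and both readings of 2.54 need fewer. That stands: a reader might infer that the SUD-control comparison is underpowered, and nothing here supports that.

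Counting controls can also be defended. The article words the rule in terms of the sample and participants, and the SUD-versus-healthy classifier does use controls. That stands for the classifier. It does not carry over to duration and relapse, whose labels controls cannot have.

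A third defence is that collected items are not network inputs. Data Preprocessing describes filter-based feature selection and mentions dimensionality reduction, and the outcomes section groups the data into four subprofiles. This disposes of a stronger reading, in which every collected item is tallied to about 46 inputs and 460 participants. That tally depends on coding choices the article does not make. What remains is that nothing fixes the input count at four; the figure appears only in the sample-size argument.

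Finally, the limitations section concedes that the algorithm may not generalise and that one suited to smaller samples might be considered. This is candid, but it supplies neither a derivation of 25 nor a size basis for the SUD-only models.

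**Conclusion.** The point holds as a wrong-as-written justification. The stated inputs give 16 to 18 per group (raw) or 3 to 5 (standardized) at two-sided 5% and 80% power, not 25. For the primary objective, 25 SUD participants fall 15 short of the rule's own minimum of 40, even with the count of four inputs accepted.

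Limits on the conclusion:

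- It is tempting to say that 2.54 *is* the pooled SD entered by mistake. The agreement with 2.536 makes this plausible, but the source study is not at hand and a mislabelled raw difference remains possible. The conclusion does not depend on it, since neither reading gives 25.
- The 93% power figure applies only if 2.54 is a real raw difference. If it is merely an SD, power at 25 is unknown.
- A reader might infer that the models must be cut to two inputs, since 25 / 10 = 2.5. The rule is a rule of thumb, and such a cap would undo the integration of four profiles that the study sets out to test. The documents do not call for it.

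**What to change.** 1. **Correct Textbox 1.** Give the mean difference taken from the source study, say whether it is raw or standardized, state sidedness, and report the n and power that those inputs produce. If 25 includes an allowance for loss, state it.
2. **Limit the scope of the two-means calculation.** Say that it supports only the SUD-control comparison.
3. **Apply the rule output by output.** State that 50 participants meet the lower bound for the SUD-versus-healthy classifier on a count of four inputs, and that 25 SUD participants do not meet it for duration and relapse. Report the latter models as exploratory unless the number of labelled SUD participants reaches the rule for the inputs actually used after feature selection.

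The cost is rewriting one paragraph and accepting a less favourable justification. No procedure or enrolment target has to change, and the existing aim of exceeding 25 can stand. The article reports 18 SUD participants enrolled as of June 2025 and recruitment open to January 2027, so the correction can be made while recruitment is still under way.
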